### Study design

The anterior approach trial is a registered [ISRCTN45066244], prospective intraoperatively randomized (expertise-based) multicenter trial of patients who will undergo elective resection for colorectal liver metastases. It is designed as a two-group parallel superiority study. As the primary objective of this study is the extent of intraoperative tumor cell dissemination we hypothesize that intraoperative tumor cell shedding can be reduced significantly in the anterior approach compared to the conventional approach group.

### Surgical Interventions

All surgical interventions in this trial follow standardised described techniques which will be shortly described below. A detailed description of all surgical techniques is also in the study protocol.

#### Incision lines

Abdominal incision can be achieved according to the preference of the surgeon. A complete exploration of the abdomen, including potential frozen sections (of suspicious lesions or lymph nodes) is performed to decide whether a curative resection is feasible. An intraoperative ultrasound evaluation of the left liver is performed. If both approaches seem possible for the surgeon randomization will be performed at this point.

#### Conventional approach

The liver will be mobilized from the retroperitoneum including the division of short venous branches to the inferior vena cava. In the next step the inflow control (either intra- or extrahepatic) is performed by ligation and division of right portal vein and hepatic artery. The outflow is controlled by ligation and division of the right hepatic vein, and possibly, middle hepatic vein. Parenchymal transection is performed according to surgeon's preference and local standards (e.g. stapler, Cusa, etc.). Optionally, Pringle manoeuvre can be performed.

#### Anterior approach

Extrahepatic inflow control is maintained by ligation and division of right portal vein and hepatic artery before any mobilization of the right liver lobe. A hanging liver manoeuvre is performed without manipulation of the right lobe [14]. Afterwards, parenchymal transaction is performed (with optional Pringle manoeuvre). This is followed by the outflow control with ligation and division of the right, and possibly, the middle hepatic vein. Finally, the short venous branches of the inferior vena cava will be divided and the liver will be mobilized out of the retroperitoneum.

Any deviation or change of the standardized operation techniques will be regarded as a protocol violation. For safety reasons, the operating surgeon is allowed to change the surgical technique at any time point during the operation.

### Sample acquisition

Blood sample: From each patient two central venous blood samples will be obtained. One blood sample (10 cc) will be drawn after induction of general anesthesia through a central venous catheter, which is routinely placed just before surgery. Immediately after resection of the liver metastases, 10 cc of central venous blood will again be taken. The intraoperative blood sample will be obtained without occlusion of the hepatoduodenal ligament. If a wedge or segmental liver resection or other organ resection is performed in addition to a right hepatectomy the intraoperative blood sample will be obtained after the right hepatectomy. Bone marrow sample: A bilateral bone marrow sample (each 10 cc) will be taken after induction of general anesthesia just prior to skin incision after disinfection from both iliac crests. Bone marrow sampling is optional for the patient.

Note: EDTA and not Heparin will be used as anticoagulant for bone marrow and blood samples.

### Sample size and statistical consideration

150 patients will be accrued to this study. Patients who underwent R1 resection and patients with an intraoperative blood loss of greater than 2000 cc will be excluded.

The sample size of this trial was calculated with regard to the previous results and data from our study on hematogenous tumor cell dissemination during resection of liver metastasis from colorectal cancer [10] and the study on the use of the anterior approach as a new liver resection technique in patients with hepatocellular carcinoma [12]. For statistical sample size calculation a 1:1 randomization in both treatment groups was assumed.

From the analysis of the previous data we expect to detect a difference of at least 30% in the proportion of intraoperative tumor cell dissemination between the two groups. The incidence of hematogenous tumor cell dissemination in the conventional group is reported to be 50–55% and it will be expected to be 15–20% in the anterior resection groups. To achieve a power of 90% (beta = 0.1) approximately 112 patients have to be recruited (two-sided test, Type I error of 5%). Due to the expectation that about 25% of all the patients will have circulating tumor cells at baseline we have to increase the total number of randomized patients to 150 patients (75 in each arm). With this sample size the study will have adequate power to address the primary objective.

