### Clinical evaluation

The clinical evaluation of the patients includes a preoperative, intraoperative and postoperative evaluation. In the preoperative evaluation the operating surgeon has to evaluate whether the liver metastasis or metastases can be resected by either technique. During the operation the operating surgeon can change the technique at any time during the procedure if necessary for the patients safety. In this case the patient will be removed from the study.

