### Analysis

We evaluate the influence of two different liver resection techniques on the incidence of intraoperative hematogenous tumor cell dissemination in patients with colorectal liver metastases. Patients with circulating tumor cells present in the bloodstream at baseline (before operation) will be excluded from the primary analysis, hence the primary endpoint is the presence of disseminated tumor cells after liver resection. Details of the timing of the different blood samples drawn from each patient are provided.

The analyses will be performed as intention to treat analyses.

An interim analysis regarding the incidence of intraoperative tumor cell dissemination between the two arms in this study will be undertaken after the randomization of the first 75 patients. If the p-value is < 0.005, the study will be terminated and it will be concluded that the anterior approach technique significantly reduces intraoperative tumor cell dissemination. If the p-value is > 0.65 the trial will be terminated and it will be concluded that there is no significant difference between the two techniques with regard to intraoperative tumor cell dissemination. For a p-value between 0.005 and 0.65, the study will be continued to the total number of 150 patients. The interim analysis is planned using the O'Brien-Fleming boundary with a provision to stop early in favor of the null hypothesis.

Primary comparison of the proportion of patients with disseminated tumor cells in the blood after liver resection will be carried out by Fisher's exact test.

Secondary endpoints as blood loss and duration time of resection will be evaluated by t-test, and amount of used blood units and complication rates will be evaluated by Fisher's exact test. Survival probabilities will be estimated by Kaplan-Meier method and groups will be compared using the log-rank test. A comparison of survival curves will be only feasible after long term follow-up, currently estimated as at least three years. Prognostic relevance of tumor cell detection in blood and bone marrow will be assessed using proportional hazards regression.

The Cochran's Q test will be performed to correlate PCR results with timing of blood collection.

Tumor cell detection rates in blood versus bone marrow samples will be compared with the Mc Nemar's test.

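### The increase from 112 to 150 patients allows only for baseline-positive patients; any further loss from the plan's other exclusions comes off the stated 90% power at 50% versus 20%

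*Protocol article*

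**What the plan says.** The section Sample size and statistical consideration of the protocol article expects rates as follows: "conventional group is reported to be 50–55% and it will be expected to be 15–20% in the anterior resection groups". It asks for a difference of at least 30 percentage points and continues: "To achieve a power of 90% (beta = 0.1) approximately 112 patients have to be recruited", with a two-sided 5% test. The only reason given for the step to 150 is this: "Due to the expectation that about 25% of all the patients will have circulating tumor cells at baseline we have to increase". The section ends by calling the resulting power adequate for the primary objective.

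Other statements bear on who is analysed:

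- **Blood loss and R1.** The same section opens with "Patients who underwent R1 resection and patients with an intraoperative blood loss of greater than 2000 cc will be excluded". The exclusion criteria in Table 1 specify that the blood-loss patients leave the analysis of tumor cells in blood, which is the primary endpoint. For R1 patients, Table 1 speaks only of leaving further follow-up and says that their data are recorded.
- **Change of technique.** Clinical evaluation says: "In this case the patient will be removed from the study". The Analysis section says that the analyses are by intention to treat.
- **Interim.** The Analysis section plans a look after 75 randomized patients, with an efficacy stop at p < 0.005 and a futility stop: "If the p-value is > 0.65 the trial will be terminated and it will be concluded that there is no significant difference". The primary test is Fisher's exact test.

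**The concern.** The sample size section names exclusions and then sizes the trial as if they removed nobody. All three depend on events after randomization (margin status, blood loss, change of technique), so the losses come on top of the baseline-positive patients. Each patient lost from the primary comparison takes the evaluable number below the 112 on which the 90% rests. The futility stop also costs some power, and the sample size section does not mention the interim analysis.

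The stake is how a null result is read. The plan allows the trial to end, at the interim or at the final analysis, with a conclusion of no significant difference. Readers would weigh that conclusion against a type II error of 10%, which holds only if the further losses are negligible.

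**Working it through.** **Inputs from the protocol.** Two-sided 5%; power 90%; 1:1 allocation; 50–55% versus 15–20%; minimum difference 30 points; 25% baseline-positive; Fisher's test; interim after 75 of 150 randomized; stop if p < 0.005 or p > 0.65.

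**Assumptions.** A further loss of 0 to 20% of baseline-negative patients, equal in both arms. A final test at p < 0.05, because the article gives no separate final level; using 0.048 instead lowers the results by less than one point.

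**Step 1: which case does 112 fit?** The only stated pair with a difference of exactly 30 points is 50% versus 20%.

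- Uncorrected normal formula, per arm: [1.960 × √(2 × 0.35 × 0.65) + 1.282 × √(0.25 + 0.16)]² / 0.30² = 51.01. This rounds up to 52 per arm, 104 in total (116 with a continuity correction).
- Exact Fisher power at 56 per arm (112 in total), without an interim, is 89.8%. A strict 90% needs 58 per arm (116).
- For 90% with Fisher's test, the other pairs need far fewer patients: 43 per arm (86) at 55% versus 20%, and 41 per arm (82) at 50% versus 15%.

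So about 112 is reproduced, on power, at 50% versus 20% and at no other stated pair.

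**Step 2: what does the increase cover?** 112/0.75 = 149.3, rounded to 150. In reverse, 150 × 0.75 = 112.5. Nothing is left for any other loss.

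**Step 3: power after further loss.** The two binomial distributions are enumerated exactly. The interim falls at half of the evaluable patients (75 × 0.75 ≈ 56, or 28 per arm with no further loss). Fisher's test is used at both looks, with both stops applied. Evaluable patients per arm = 56 × (1 − loss), rounded.

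| Further loss (assumed) | Per arm | 50% vs 20%, no interim | 50% vs 20%, with stops | 55% vs 20%, with stops | 50% vs 15%, with stops |
|---|---|---|---|---|---|
| 0% | 56 | 89.8% | 88.3% | 95.6% | 96.8% |
| 5% | 53 | 87.8% | 86.3% | 94.7% | 95.9% |
| 10% | 50 | 85.3% | 83.4% | 92.9% | 94.6% |
| 15% | 48 | 83.1% | 81.2% | 91.5% | 93.5% |
| 20% | 45 | 81.5% | 79.0% | 89.7% | 91.8% |

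At 55% versus 15%, power with both stops is 96.8% even at 20% loss. Rounding the numbers per arm or at the interim the other way moves the results by about half a point.

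**Step 4: share due to the futility stop.** At 50% versus 20% with no further loss, the interim rules cost 89.8 − 88.3 = 1.5 points, and the chance of a wrong futility stop is about 4%. At 20% loss they cost about 2.5 points and that chance is about 8.6%. Most of the fall therefore comes from lost patients.

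**The case against.** **The loss rate is not in the plan.** A reader might infer that the trial's power is 79–86%. The protocol does not support that. The range comes from an assumed 5–20% further loss, and nothing in the article says how often R1 resection, heavy blood loss or a change of technique is expected. This objection stands: the figures show sensitivity to loss and are not the plan's own power.

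**Only the least favourable pair falls short.** This also stands. At the other stated rates, power is about 90% or more even at 20% loss. But 112 fits only 50% versus 20%, and the section sizes for a difference of at least 30 points, so the stated 90% has to be judged at that pair.

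**Two of the three exclusions may remove nobody from the primary analysis.** Table 1 takes R1 patients out of follow-up only, and the primary blood sample is drawn immediately after resection. Removing patients whose technique is changed conflicts with intention to treat. It is fair to call these contradictions rather than settled losses. The blood-loss rule does reach the primary endpoint, and it has no allowance.

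**The interim may already be covered.** A reader might infer that 112 is a fixed-sample figure that ignores the interim. That cannot be established. The uncorrected total of 104, multiplied by a normal-theory inflation of about 1.03–1.04 for these boundaries, gives 107–109, and the article says only approximately 112. The full calculation is not shown.

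**The claim for 150 is adequate power, not 90%.** True, but the 90% is the only figure given. It would be too strong to call it false: with no further loss the result is about 88%.

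**Conclusion.** The point holds in a limited form. The arithmetic in the sample size section is sound for the one loss that it names; the defect is that the plan's other exclusions have no stated allowance. At 50% versus 20%, with Fisher's test and both interim stops, power is about 88% if nobody else is lost. It falls by roughly 2 to 3 points for each further 5% of baseline-negative patients lost, reaching about 79% at 20%. At a loss of 15–20% the type II error is 19–21%, about twice the stated 10%.

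These figures rest on the assumed loss rates, on equal loss in the two arms and on a final test at 5%. They do not show that the trial is underpowered across its stated range of rates. Nor do they show that the futility stop was left out of the calculation or that recruitment must rise. The point is worth correcting because the remedy is cheap.

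**What to change.** 1. Reconcile Table 1 with the sample size section on R1 and blood-loss patients, and Clinical evaluation with the Analysis section on patients whose technique is changed. The primary analysis should follow the stated intention to treat and keep every randomized baseline-negative patient with a blood sample, in the arm assigned. Restricting to baseline-negative patients is compatible with this, because the baseline sample is drawn before randomization.
2. Restate power as about 88% at 50% versus 20% with about 56 evaluable patients per arm, Fisher's test and the stated interim stops.
3. If any exclusion stays, give its expected rate with its source, and the resulting power at 50% versus 20%.

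The cost is a short change to the text. No additional patients and no change of primary test are needed. The Current status section reports 61 randomized patients, so when the article was written the change could still be made before the interim at 75.

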### Randomisation, stratification and blinding

The study is conducted in a prospective randomized manner. After giving informed consent and inclusion into the study, patients will be randomized in the operating room after surgical exploration just prior to resection by using sealed opaque serial numbered envelopes. These envelopes will be supplied by the Clinical Trials Centre (KSC) of the Department of Surgery, University of Heidelberg. The patients will be randomized 1:1 into each arm of the two different liver resection techniques. As stratification factors, the participating institution and the Fong score will be used [15]. The Fong score predicts the risk of recurrence after surgical resection of colorectal metastases to the liver. Two strata will be used (Fong score 0–2 and 3–5).

### Endpoints

As primary endpoint, we choose the tumor cell detection rate in blood samples obtained intraoperatively using a CK 20 RT-PCR. The method is already established and this was the endpoint for the sample size calculation and further decision making. As secondary endpoints, overall survival and disease-free survival will be recorded during the follow-up in both groups. Further secondary endpoints are blood loss, duration time of resection, number of blood products transfused, prognostic relevance of tumor cell dissemination to the bone marrow, and postoperative complications. All these parameters will be collected prospectively as part of the study protocol.

### Laboratory workup

The processing of blood and bone marrow samples will be done in each participating institution using a standard protocol. After processing, samples will be stored at -80°C for further laboratory workup which will be centrally performed at the Department of Surgery, University of Heidelberg. The samples from participating institutions will be sent to the laboratory at the Department of Surgery, University of Heidelberg by overnight service on dry ice. The samples will be accompanied by positive controls to ensure quality of processing and mailing of the samples. Blood and bone marrow samples will be analyzed by a CK 20 RT-PCR as previously described [7].

#### RT-PCR

All PCR reactions will be accompanied by positive and negative controls to ensure adequate performance of the procedure. Two investigators independently judge the results of the PCR. In case of different judgment (which in case of RT-PCR virtually never happens), the PCR result will be confirmed by hybridization.

The laboratory workup of all samples will be centrally performed in the Department of Surgery, University of Heidelberg. The technician working up the sample and the physician analyzing the test results are blinded for clinical data of each patient

### Clinical evaluation

The clinical evaluation of the patients includes a preoperative, intraoperative and postoperative evaluation. In the preoperative evaluation the operating surgeon has to evaluate whether the liver metastasis or metastases can be resected by either technique. During the operation the operating surgeon can change the technique at any time during the procedure if necessary for the patients safety. In this case the patient will be removed from the study.

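### Removing patients whose technique is changed during surgery contradicts the stated intention-to-treat analysis and can bias the comparison, in a direction the documents do not settle

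*Protocol article*

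**What the plan says.** All of this is in the protocol article.

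- Randomisation, stratification and blinding: "patients will be randomized in the operating room after surgical exploration just prior to resection". Allocation is 1:1.
- Anterior approach: "For safety reasons, the operating surgeon is allowed to change the surgical technique at any time point during the operation". The same paragraph adds: "Any deviation or change of the standardized operation techniques will be regarded as a protocol violation". It says nothing about removal.
- Clinical evaluation, on a change of technique for the patient's safety: "In this case the patient will be removed from the study".
- Analysis: "The analyses will be performed as intention to treat analyses". No exception is made for a change of technique.
- Table 1 lists exclusions for R1 resection and for blood loss of 2000 cc or more, and says in each case what is kept. R1 patients' data are recorded, and patients with high blood loss stay in all analyses except that of tumour cells in blood. A change of technique is not in the list.

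**The concern.** A change of technique happens after randomisation and is decided by someone who knows the arm. Dropping patients because they did not receive the assigned technique is what an intention-to-treat analysis is meant to prevent. The rule carries no reservation of the kind that Table 1 attaches to its own exclusions. Read as written, it takes the patient out of the primary endpoint and out of every secondary comparison.

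Two things are at stake. If the frequency of changes, or the kind of patient in whom they occur, differs between arms, the retained groups are no longer comparable. In addition, the article's Conclusion promises information on the safety of each technique, and patients in whom a technique was abandoned for safety bear directly on that question.

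**Working it through.** **Inputs from the protocol article.** Sample size section: conventional rate 50–55%, anterior rate 15–20%, a difference of at least 30 points, 90% power, two-sided 5%, about 112 evaluable patients, 150 randomised after a 25% allowance. Analysis section: Fisher's exact test. I use 50% against 20%, which gives the 30-point difference, and 56 evaluable patients per arm.

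**Assumed, because the documents give no figure.** c is the share of an arm whose technique is changed (5–20%). q is the positivity of those patients.

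**1. The plan's own figure.** Exact two-sided Fisher power with 56 per arm at 50% against 20% is 89.8%. The normal approximation gives 104 patients in total without and 116 with continuity correction, which bracket 112. Then 112 / 0.75 = 149.3, rounded up to 150. The sample size reproduces and is not in dispute. The 25% allowance covers baseline-positive patients only, so nothing is set aside for removals.

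**2. Anterior patients converted, under the protocol's own hypothesis.** The Background argues that more manipulation gives more shedding. Let converted anterior patients have the conventional rate, q = 50%, and the others 20%. The intention-to-treat anterior rate is (1 − c) × 0.20 + c × 0.50. After removal it is 20% whatever c is, so the difference stays at 30 points.

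| c | Anterior rate, ITT | Difference, ITT | Exaggeration by removal | Fisher power, ITT | Fisher power, removal |
|---|---|---|---|---|---|
| 5% | 21.5% | 28.5 | 1.5 | 85.8% | 90.2% |
| 10% | 23.0% | 27.0 | 3.0 | 80.9% | 89.3% |
| 15% | 24.5% | 25.5 | 4.5 | 75.2% | 89.0% |
| 20% | 26.0% | 24.0 | 6.0 | 68.9% | 87.2% |

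Differences are in percentage points.

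**3. Conventional patients changed to anterior.** With c = 10% and q between 20% and 35%, the intention-to-treat conventional rate is 0.9 × 0.50 + 0.1 × 0.20 = 47.0% up to 0.9 × 0.50 + 0.1 × 0.35 = 48.5%, against 50% after removal. The contrast again widens, by 1.5 to 3 points.

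**4. Where the direction changes.** Suppose technique has no effect (50% in both arms) and removal is from the anterior arm only. The bias towards anterior is c(q − 0.50)/(1 − c).

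- c = 10%, q = 90%: 0.10 × 0.40 / 0.90 = +4.4 points.
- c = 10%, q = 50%: 0.
- c = 10%, q = 20%: 0.10 × (−0.30) / 0.90 = −3.3 points.
- c = 20%, q = 90%: 0.20 × 0.40 / 0.80 = +10 points. The Fisher type I error is then 15.7%, against 2.9% under intention to treat.

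The sign also reverses at 50% against 20% if the removed patients are difficult conventional cases that shed heavily. With c = 10% and q = 70%, the conventional rate is 0.9 × 0.50 + 0.1 × 0.70 = 52% under intention to treat and 50% after removal, so the contrast narrows by 2 points.

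**5. Removal also costs power.** If 10% are removed from both arms, 50 per arm remain and Fisher power at 50% against 20% is 85.3%.

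**The case against.** Much in the design limits conversions. The surgeon must judge both techniques feasible on preoperative imaging and again at exploration before the patient is randomised. Recruiting surgeons need at least 25 successful liver resections, and operation records are reviewed centrally for violations. For the primary endpoint, patients who lose 2000 cc or more are already left out of the blood-sample analysis, so the worst-bleeding conversions would be missing from it in any case. These points stand. Conversions may be few and the bias small. They do not remove the contradiction, and the last one does not protect the secondary endpoints.

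A reader might go further and infer that the bias most likely favours the anterior approach. The conventional sequence begins with mobilisation, so switches might run mainly from anterior to conventional. The documents do not support more than plausibility here. They allow a change in either arm and give neither conversion rates by arm nor outcomes of converted patients.

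Larger figures can be produced, but only by choice of inputs. With c = 20%, q = 70% and an overall anterior rate of 20%, removal lowers that rate by 12.5 points. The retained patients would then be at (0.20 − 0.14)/0.80 = 7.5%, well below the 15–20% the protocol expects. With no true effect, c = 5–20% and q = 50–70%, a common rate of 35% gives an apparent anterior advantage of 0.8 to 8.8 points. But 35% lies below the protocol's control rate and below every assumed q, so the sign is built in. At 50% in both arms the same inputs give 0 to 5.0 points, and at 55% they give −1.3 to +3.8.

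A reader might also think that the Anterior approach paragraph is a third conflicting statement. It is not. A change of technique can be a protocol violation whether or not the patient is then removed.

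**Conclusion.** The point holds as a contradiction between two stated rules: removal in Clinical evaluation and intention to treat in Analysis. Nothing elsewhere in the article resolves it, and it decides who is in the primary analysis, so it needs an amendment.

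The bias is a risk whose direction and size the documents do not fix. The protocol's own hypothesis points to an exaggerated contrast: 1.5 to 6 points if 5–20% of anterior patients convert at 50% positivity and the others are at 20%. That range rests on assumed conversion and positivity figures, and other equally undocumented assumptions reverse it. Confidence is high for the contradiction and low for any particular direction or magnitude.

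**What to change.** Reconcile Clinical evaluation with Analysis by replacing the removal sentence with, for example: *The patient stays in the study, has the planned samples and follow-up, and is analysed in the arm assigned at randomisation; the change is recorded as a protocol violation.* Any analysis without these patients should be a per-protocol analysis labelled as a sensitivity analysis. This concerns the analysis set only and leaves the surgeon's freedom to change technique as it is.

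The article reports 61 patients randomised, with the interim analysis due after 75. For any of the 61 already removed under this rule, sample results, operative data and follow-up should be recovered where possible, before the interim analysis, which can stop the trial.

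The amendment is one sentence plus that data retrieval. The statistical cost should be stated openly, because it is not slight if conversions are common. On the assumptions of step 2, power under intention to treat is about 86% at 5% anterior conversion, 81% at 10% and 69% at 20%, against the planned 90%. The higher power after removal belongs to a contrast among selected patients and is no reason to keep the rule.
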